### 2.3. Recruitment and Randomization

Participant recruitment will take place at the Physical Medicine and Rehabilitation Service of Virgen de las Nieves University Hospital in Granada (belonging to the Andalusian Health Service). Individuals referred to the Rehabilitation Unit by their medical specialist and placed on a waiting list will receive information about the possibility of participating in this RCT via email or a telephone call. The diagnosis of CPLBP will be conducted by medical specialists in Physical and Rehabilitation Medicine, with advanced training and extensive clinical experience in musculoskeletal disorders. Subsequently, those initially interested in participating will be invited to an informational session where the study will be explained, and any concerns that may arise will be addressed. The estimated recruitment period for selecting participants will be from 1 to 3 months. Additionally, all interested individuals will be provided with written information about the study.

Individuals who agree to enroll in the study will be asked to read and sign a written informed consent that allows them to withdraw at any time. A unique code will be assigned to each participant to ensure their anonymity. On the first evaluation day, participants will report to the Multidisciplinary Laboratory in the Faculty of Sport Sciences (Granada) and will complete the following assessments: clinical information survey, blood pressure, resting heart rate, body composition, pain threshold, physical fitness, and gait parameters. The initial survey (anamnesis) will be conducted through face-to-face interviews by trained staff in order to collect data on sociodemographic characteristics (age, marital status, educational level, and current occupation), medical records and comorbidities, medicine consumption, and health habits (tobacco, alcohol, etc.). The Spanish version of the PAR-Q (C-AAF) [40] will be used to detect individuals who should undergo a medical examination before doing any type of PA. Individuals will not be required to perform any additional physical exercise or receive treatment for CPLBP upon starting this RCT. Participants will receive an accelerometer and several health-related questionnaires to complete at home on the same day of the evaluation. Participants will be asked to return the accelerometer and questionnaires nine days later. As a reward, they will receive a report for each assessment they attend.

Once the baseline evaluations have been completed, participants will be randomized into different groups to reduce the risk of bias during the assessment. A computer-generated randomization sequence stratified by two factors (age at study entry and sex) will allocate participants to each group. This randomization sequence will be created by a blinded researcher external to the project using computer software. The allocation will be concealed in a password-protected computer file.

The groups will undergo pre-test (before the intervention), post-test (after each intervention), and follow-up (after an 8-week detraining period) measurements.

### 2.4. Intervention

The intervention program will be conducted face-to-face in groups at the Physical Medicine and Rehabilitation Service. Each session will have a maximum of 17 participants. To accommodate participants’ availability, all intervention groups will offer morning and afternoon sessions. The physical exercise program will be supervised and guided, and all sessions will be conducted under the direct supervision of licensed (MD and Ph.D.) physical therapists and sports sciences specialists present physically. Mindfulness sessions will be taught by a professional accredited by Brown University who will not participate in any assessment phase. All the professionals will have experience working with this population. The supervised exercise program will be applied by adapting rehabilitation exercise methods used in previous literature [32,35] and will be analyzed with the Consensus on Exercise Reporting Template (CERT) [36]. This guide consists of 16 items that describe information about the performance of an exercise intervention program. This facilitates its development, guidance, evaluation, interpretation, and clinical use. The program will report the FITT exercise principles (frequency, intensity, time, and type) as a detailed and high-quality physical exercise intervention.

The program will follow National Strength and Conditioning Association [37] and American College of Sports Medicine [41] recommendations, suggesting 6 to 12 repetitions per muscle-strengthening PA at moderate-to-vigorous intensity, equivalent to >5 on the Rating of Perceived Exertion (RPE) scale (1 ‘no effort’ to 10 ‘maximal effort’) [42].

The IG1 (supervised exercise program) will undergo an exercise program twice per week (45 min per session) for 8 weeks. Each session will include a warm-up (5 min), muscle-strengthening exercises (35 min), and a cool-down (5 min, stretching exercises). The program will focus on core muscles, starting with low-intensity isometric contraction for trunk stabilization and mobility exercises, then increasing intensity with functional tasks. Exercise intensity will be moderate-to-vigorous, assessed via the RPE scale [42], ensuring no pain is felt. This scale will be visible to participants during sessions. Each exercise will last 60 s, followed by 60 s rest. Execution speed will be individualized to each participant’s physical condition and tolerance. Exercises will follow a fixed order with progressive difficulty, as described in previous literature [32,43]. This progression will be structured according to the following phases [32]. (i) *Phase 1* (3 sessions, ≥5 RPE): mobility, isometric, and motor control exercises that will include full body, with special emphasis on the core, particularly isometric contraction of the transversus abdominis muscle. Participants will be instructed to place their hands on the lower abdomen during the exercises to perceive the contraction through kinesthetic feedback and facilitate correct transversus abdominis activation (ii) *Phase 2* (4 sessions, ≥5 RPE): co-contraction and functional tasks involving deep trunk muscles. (iii) *Phase 3* (4 sessions, ≥6 RPE): functional task with greater difficulty or intensity, including load. (iv) *Phase 4* (5 sessions, ≥6 RPE): functional task performed on an unstable surface.

A detailed description of the exercise intervention is shown in Table 3 and Table 4. Participants will receive real-time feedback on posture correction and examples for exercise familiarization. Strategies to improve exercise adherence will include: (i) a positive and dynamic session environment; (ii) an attendance control system to minimize dropouts.

The IG2 (multidimensional program) will follow the same exercise protocol as IG1 (twice per week, 45 min per session) and also participate in a mindfulness program once per week (2.5 h per session) for 8 weeks. The MBSR program will follow Jon Kabat-Zinn’s protocol [44]. Each session will include a topic presentation, group dialogue and exploration (using appreciative inquiry), and a mindfulness practice. Participants will receive workbooks, guided meditation audios, and instructions for home practice. Details are provided in Table 5.

**Table 5 healthcare-13-02065-t005:** Overview of the Mindfulness-Based Stress Reduction (MBSR) program.

Session	Content Description	Class Details	Session	Content Description	Class Details
1	- Brief history of the MBSR program. Definition and scientific evidence. - What mindfulness is and is not. - Example of a standard mindfulness practice. - Guided reflection: “What brought you here?” - Introduction of participants and instructor. - Raisin meditation. - Body scan. - Presentation of home practice. - Closing practice.	Introduction session 2.5 h Individual practice Face-to-face Chairs	2	- Opening practice. - Standing yoga postures. - Body scan. - Group dialogue (small and large group). - 9-point exercise: conditioning and creative response. - Seated meditation with attentional focus. - Presentation of home practice. - Closing practice.	Introduction session 2.5 h Individual and group practice Face-to-face Chairs, mats
3	- Opening practice. - Focused attention meditation. - Floor yoga postures. - Dialogue on personal experience. - Review of the Pleasant Events Calendar (awareness of bodily sensations, thoughts, emotions). - Presentation of home practice. - Closing practice.	2.5 h Individual and group practice Face-to-face Chairs, mats, notebook	4	- Opening practice. - Standing yoga postures. - Seated meditation focusing on unpleasant experiences (pendulum method). - Dialogue and reflection. - Review of the unpleasant events calendar and link with stress. - Explanation of stress physiology and reactivity.Presentation of home practice. - Closing practice.	2.5 h Individual and group practice Face-to-face Chairs, mats, notebook
5	- Opening practice. - Standing yoga postures. - Full meditation alternating focus points (open awareness). - Dialogue on progress, challenges, and expectations. - Introduction to the habit loop and the mindful pause. - Presentation of home practice. - Closing practice.	2.5 h Individual and group practice Face-to-face Chairs, mats	6	- Opening practice. - Standing yoga postures. - Extended seated meditation, with more silence and less guidance. - Dialogue on practice engagement and outcomes. - Guided reflection on a difficult communication situation and interactive dialogue. - Presentation of home practice. - Closing practice.	2.5 h Individual and group practice Face-to-face Chairs, mats
7	- Opening practice. - Movement practice: simplicity and boundary exploration. - Seated meditation (extended silence). - Dialogue on experience. - Reflection on relationship with technology and its impact. - Presentation of home practice. - Closing practice.	2.5 h Individual and group practice Face-to-face Chairs, mats	8	- Opening practice. - Body scan. - Group dialogue on home practice. - Writing a letter to the “future self”. - Resources for long-term practice (“the rest of your life”). - Sharing of final reflections and program integration. - Closing practice.	2.5 h Individual and group practice Face-to-face Chairs, mats, notebook

The Mindfulness-Based Stress Reduction program is based on previous evidence [44,45]. Each session includes a topic presentation, group dialogue and exploration, and a mindfulness practice.

The CG will receive the usual care provided by the Physical Medicine and Rehabilitation Service. Participants will follow the same session structure described above twice per week (45 min per session) for 8 weeks. All participants will perform 1 set of 10 repetitions or 60 s per exercise, followed by 60 s of rest. Execution speed will be individualized. Intensity will be assessed with an RPE scale (≥5 RPE). Sessions will include: warm-up (5 min: postural awareness, diaphragmatic breathing, costal breathing, transversus abdominis contraction, pelvic swing); main activity (35 min: lower/upper abdominis exercise, hip abduction with knee extension, cat-camel exercise, alternate arm/leg elevation in quadruped, bird-dog); and cool-down (5 min: lumbosacral, psoas, hamstring, and pyramidal muscle stretching, bird-dog, and lumbosacral stretching on the floor). All of them will be performed in supine or quadrupedal position. Although active, this protocol reflects hospital standard rehabilitation care. Including it in the control group meets ethical and organizational requirements, ensuring participants are not deprived of care, allowing a more rigorous comparison with the multidimensional intervention.

This program allows adaptations for practical evidence-based aspects, such as performing an alternative exercise targeting the same muscle group without causing pain or changing the plane of movement. Adverse events, effects, or health issues attributable to the testing or intervention sessions, along with their severity and resolution, will be recorded by a researcher responsible for auditing the assessment team. If an adverse event prevents participation, temporary or permanent exclusion will be discussed and documented. Temporary exclusions require medical clearance for return.

This study was approved by the Clinical Research Ethics Committee of Granada, Government of Andalusia, Spain (code: 2255-N-21). It will be conducted following the ethical principles of the Declaration of Helsinki (1964 and later amendments). No formal audit is scheduled for this clinical trial.

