### 2.2. Participants

This RCT, based on a supervised exercise program and mindfulness intervention, was prescribed and planned by physical therapists and sports science professionals, and it will be conducted in Granada (southeastern Spain). Based on previous literature [22], with a statistical power of 0.80, an alpha error of 0.05, and an effect size of 0.70, a sample size of 26 participants per group is sufficient to find differences in pain after the intervention. Considering a dropout rate of approximately 20–30%, as reported in similar studies involving pain populations [39], the total sample size will be set at 105 participants, randomly assigned to intervention group 1 (IG1, *n* = 35), intervention group 2 (IG2, *n* = 35) and control group (CG, *n* = 35). The inclusion and exclusion criteria are described in Table 2.

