## 4. Statistical Analysis

Since this study aims to determine the potential efficacy and effectiveness of supervised exercise programs and mindfulness, statistical analysis will be performed using both per-protocol and intention-to-treat approaches (with ≥70% attendance required for inclusion). The effects of the intervention will be assessed as between-groups differences in changes from baseline to post-intervention in primary and secondary outcomes using one-way analysis of covariance (ANCOVA). The mean change (post-intervention minus baseline values) will be used as the dependent variable, the group as the fixed factor, and the baseline value of the outcome as a covariate. The same approach will be applied to evaluate the persistence of changes at follow-up. Given the repeated-measures design, linear mixed models will also be used to examine group-by-time interactions across all time points. This approach accommodates missing data under the missing-at-random assumption and accounts for within-subject correlation, providing a more robust framework than ANCOVA for longitudinal analyses. All analyses will be adjusted for potential confounding variables that are not well balanced at baseline. Sex will be used as a potential covariate in all analyses to explore whether the intervention effects differ between men and women, and whenever possible, the sample will be stratified by sex. Cohen’s d will be calculated to determine standardized effect sizes. To control for type I error due to multiple comparisons, the Bonferroni correction will be applied when conducting post hoc analyses or when evaluating multiple outcome variables. Statistical significance will be set at α = 0.05. All analyses will be performed using the Statistical Package for the Social Sciences (SPSS) for Windows, Version 27.0. (IBM Corp., Armonk, NY, USA).

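### Eligibility does not require candidates to be able to attend every arm's timetable, so non-attendance may depend on arm, and the 70% attendance condition could turn it into selective exclusion from IG2

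*Protocol article*

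**What the plan says.** The order of events is set out in section 2.3 of the protocol article. Patients on the waiting list are contacted, and those interested are "invited to an informational session where the study will be explained, and any concerns that may arise will be addressed". They then give consent and complete baseline. After that: "Once the baseline evaluations have been completed, participants will be randomized into different groups".

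Section 2.4 sets the workload. IG1 and the control group each have two 45-minute classes a week for 8 weeks. IG2 has the same exercise classes plus a "mindfulness program once per week (2.5 h per session) for 8 weeks". On fitting sessions to participants, the section says: "availability, all intervention groups will offer morning and afternoon sessions".

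Table 2 lists five inclusion criteria: diagnosis, age, understanding of the consent and the study aim, independent movement, and ability to report problems during testing. None concerns the timetable. The nearest exclusion criterion is medical. The flexible scheduling mentioned in section 5.1 applies to assessments, not to classes.

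Section 2.2 plans for one dropout range, 20–30%, without distinguishing arms. Section 4 attaches a condition to the per-protocol and intention-to-treat approaches: "with ≥70% attendance required for inclusion". The abstract places the same condition directly after intention-to-treat.

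**The concern.** A candidate may be free for two short classes a week but not for a further 2.5 h block. Nothing in the listed criteria keeps that person out of the randomisation. Drawn to IG1 or the control group, the person can attend fully. Drawn to IG2, the person may miss the mindfulness component or withdraw.

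If that happens to any extent, loss is tied to arm and probably to work and family circumstances, which may be related to pain and disability. It would fall on IG2, the arm expected to do best under the trial's main hypothesis. The attendance condition matters most here, because it can remove such people from the analysis even when their outcomes were measured. The mixed models planned under missing at random do not bring back people whom an attendance rule has excluded.

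**Working it through.** **Workload (section 2.4).**
- IG1 and control group: 2 × 8 = 16 sessions; 16 × 0.75 h = 12 h; 1.5 h a week.
- IG2: 16 + 8 = 24 sessions; 12 + 8 × 2.5 = 32 h; 4.0 h a week.
- Ratio of weekly hours: 4.0 / 1.5 = 2.7.

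**Attendance condition (section 4).** The article does not state the denominator. Assume that all scheduled sessions count.
- IG1 or control group: 0.70 × 16 = 11.2, so 12 sessions are needed.
- IG2: 0.70 × 24 = 16.8, so 17 sessions are needed.
- All exercise and no mindfulness: 16/24 = 66.7% in IG2 (fails); 16/16 = 100% in IG1 or the control group (passes).
- 12 of 16 exercise classes: passes in IG1 or the control group; in IG2 the same person also needs 17 − 12 = 5 of the 8 mindfulness sessions.
- The margin is narrow at the top: all exercise plus one mindfulness session is 17/24 = 70.8% and passes.

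**The plan's own sample size (section 2.2).** With d = 0.70, alpha 0.05 and power 0.80, a two-sample t test needs 25.9, so 26 per group one-sided, which reproduces the stated figure. Two-sided it needs 33.02, so 34. Sidedness is not stated, so both are shown below. For dropout, 26 / 0.75 = 34.7, so 35 per arm matches the 25% midpoint of the stated range.

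**Power with extra loss in IG2.** Let q be the extra share of IG2 lost because of the timetable (assumed; the article gives no figure). IG1 keeps 35 × 0.75 = 26.25. IG2 keeps 26.25 × (1 − q). Two-sample t test, d = 0.70, alpha 0.05:

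| q | IG2 remaining | Power, two-sided | Power, one-sided |
|---|---|---|---|
| 0 | 26.25 | 70.1% | 80.4% |
| 10% | 23.6 | 67.7% | 78.5% |
| 20% | 21.0 | 64.8% | 76.1% |
| 30% | 18.4 | 61.4% | 73.2% |

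The fall due to q is 2.4 to 8.7 points two-sided and about 2 to 7 points one-sided. The gap between 80% and 70% in the first row comes from sidedness, not from the timetable.

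**Shift in the IG2 mean.** If a share q is removed and those removed differ from those who remain by δ SD, the mean of those who remain differs from the full-arm mean by q × δ. With δ assumed at 0.3–0.5:
- q = 10%: 0.03–0.05 SD.
- q = 20%: 0.06–0.10 SD.

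The direction is not known. Against the design effect, 0.10 / 0.70 = 14% at the upper end and 0.03 / 0.70 = 4% at the lower.

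**The case against.** The strongest reply is that this is largely an argument from silence in a condensed article. Scheduling details may sit in the full protocol. Candidates hear the study explained and can raise concerns before consent, so some who could not manage the longer timetable would decline. The heavier load is inherent in an add-on arm, and under a true intention-to-treat analysis non-attendance is part of that arm's effect. The values of q and δ are assumptions, and the planned 20–30% dropout may already include timetable losses. Correcting the attendance condition would remove most of the exclusion route.

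Much of this stands, and it makes the point a risk and not a demonstrated defect. It does not dispose of it. Table 2 is presented as the eligibility criteria, and ability to attend any arm is an eligibility matter that has to be settled before randomisation. The information session is not described as an availability check. As the attendance condition is now worded, non-attendance can lead to exclusion.

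Three stronger readings are tempting and are not supported:
- **Slots are assigned only after allocation.** The article says that morning and afternoon sessions are offered. It does not say when people are placed in them.
- **The control group has no choice of slot.** Sections 2.1 and 2.2 use the term intervention group for IG1 and IG2 only. However, section 2.4 speaks of all such groups, and Table 3 sets out the intervention programme with the control group included. The wording does not establish an exclusion.
- **Each arm is one place short.** From "Each session will have a maximum of 17 participants" and 35 per arm, a reader might compute 2 × 17 = 34 places. That needs exactly two classes per arm, and the number of classes is not stated.

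Nor do the documents show that people will leave IG2 while remaining in the other arms. No dropout figure by arm is given.

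**Conclusion.** The point holds as a risk that is cheap to reduce. The listed criteria do not require availability for every arm's timetable, no check before randomisation is described, and the arms differ by a factor of 2.7 in weekly hours. Non-attendance may therefore differ by arm, and the attendance condition could make it selective exclusion from IG2.

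The likely size is modest: about 2 to 9 points of power for IG2 versus IG1, and a shift of 0.03–0.10 SD in the IG2 mean. These figures rest on assumed extra losses (10–30% for power, 10–20% for the shift) on top of 25% dropout, and on an assumed outcome difference of 0.3–0.5 SD. The 66.7% against 100% contrast rests on counting all sessions in the attendance denominator. This is a worthwhile improvement to the design. It does not invalidate the trial.

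**What to change.** At the information session, before baseline assessment, show each candidate all three timetables and confirm that they could attend whichever arm is drawn, including the weekly 2.5 h mindfulness block. Add this to the inclusion criteria in Table 2. Record the preferred morning or afternoon slot before allocation, so that the preference cannot depend on the arm drawn.

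The cost is one screening question and one criterion. Some candidates who could manage only the shorter timetable would not be enrolled, so recruitment would be slightly slower and the sample slightly narrower. That narrowing should be acknowledged, because section 5.1 says that the criteria were chosen to reflect real-world patients.

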### 5.2. Limitations

Despite its potential, this protocol presents several potential limitations. First, the study design does not include a control group without treatment due to ethical considerations related to patient care in the clinical setting. The study recognizes the potential risk of participant fatigue due to using multiple assessment instruments. To mitigate this, assessments will be scheduled with sufficient time, short breaks will be provided as needed, and participants will be instructed to respond carefully. Additionally, the chosen instruments are widely used and validated in clinical research involving chronic pain populations, ensuring their relevance and feasibility. Due to limited human resources, it will not be possible to implement blinded assessment in this study. Specifically, the same team members responsible for the intervention delivery will also be involved in outcome assessment, making it unfeasible to separate these roles. This represents a potential source of performance and detection bias. Although this limitation cannot be fully mitigated, we will apply standardized procedures for data collection and outcome assessment to minimize bias and ensure reliability. To enhance internal validity, future trials should aim for blind assessors where feasible and recruit larger and more diverse samples to increase generalizability. Furthermore, upcoming research should prioritize the addition of a no-treatment control group to clearly isolate the specific effects of combined mindfulness and exercise interventions.

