### 5.3. Post-Trial Care and Dissemination Policy

The interventions involved in this trial are expected to cause no or minimal harm. No harm or compensation is anticipated for participants enrolled in the trial. The results obtained will be disseminated in the form of scientific papers, presentations at national and international conferences, as well as knowledge transfer activities for healthcare professionals.

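### Attribution to a session or test acts as a filter before an adverse event is recorded, so any safety statement or comparison by arm could be biased in an unknown direction

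*Protocol article*

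**What the plan says.** Section 2.4 (Intervention) gives the recording rule: "Adverse events, effects, or health issues attributable to the testing or intervention sessions, along with their severity and resolution, will be recorded". Severity and resolution are named as things to record. Relatedness is not, because it has already been used to select the events.

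The same sentence assigns the task: events "will be recorded by a researcher responsible for auditing the assessment team". Section 2.4 then adds "If an adverse event prevents participation, temporary or permanent exclusion will be discussed and documented", which carries no condition on cause, and later says "No formal audit is scheduled for this clinical trial".

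Three other places bear on the rule:

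- Section 5.2 (Limitations) says "it will not be possible to implement blinded assessment in this study" and that "the same team members responsible for the intervention delivery will also be involved in outcome assessment".
- Section 5.3 says "The interventions involved in this trial are expected to cause no or minimal harm".
- Section 2.4 describes a part of the combined arm (IG2) that takes place outside sessions: "Participants will receive workbooks, guided meditation audios, and instructions for home practice".

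**The concern.** Good practice is to record every event first and judge its cause second, so that the judgement can be inspected and revised. Here the order is reversed. An event that nobody links to a session or a test need not be written down, and an event never written down cannot be reclassified later.

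This matters more when judgements of cause are open to influence. The trial has no blinded assessment, those delivering treatment also assess outcomes, and the article states in advance that it expects little harm. The arms also differ in ways that could affect how readily an event is blamed on the programme. IG1 and IG2 progress to loads and unstable surfaces, whereas Section 2.4 places all control exercises in supine or quadrupedal positions. IG2 alone has mindfulness sessions and home practice.

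At stake is any statement that the programmes were safe, and any table of events by arm. A low count could come partly from the rule, and a difference between arms could reflect differences in attribution.

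**Working it through.** The article gives no adverse-event figure, so there is none to reproduce. The check has three parts.

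**1. What would still be captured under the rule**

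| Source in the article | What it would catch without a judgement of cause | What it would miss |
|---|---|---|
| Numerical pain rating before and after each session (Section 3.1.1, Perceived Acute Pain); pain scales at baseline, during the intervention, t1 and t2 (Table 1) | Pain worsening within a session, or a flare still present at the next session or assessment | Flares that settle in between; non-pain events; cause, severity and resolution |
| Clinical information survey at baseline and t2 (Table 1); Section 2.3 describes the initial one as covering medical records, comorbidities and medicines | Possibly new health problems by t2, if the repeat has the same content, which is not stated | Timing, severity and resolution of individual events |
| Documented exclusion decisions (Section 2.4) | Events that prevent participation, whatever their cause | Events that do not prevent participation |

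These are partial traces. None is a record of all adverse events. IG2 home practice is part of the intervention but is not a session. The 8-week detraining period has no sessions. Events in either setting therefore meet the literal rule only if someone links them to a session or a test.

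**2. Scheduled contact by arm (Section 2.4)**

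- IG1 and control: 2 per week × 8 weeks = 16 sessions; 16 × 0.75 h = 12 h.
- IG2: 16 + 8 = 24 sessions; 12 h + 8 × 2.5 h = 12 + 20 = 32 h.
- Ratios: 24/16 = 1.5 by sessions; 32/12 = 2.67 by hours.

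These ratios describe the opportunity to attribute an event to a session. They say nothing about how often that happens.

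**3. How a filter of this kind can act (assumed values)**

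Recorded risk = true risk × probability that an event is judged attributable. Take two arms of 35 (Section 2.2) with the same true risk. The true risk cancels in the ratio, so the recorded risk ratio depends only on the two attribution probabilities. The event counts below use an assumed true risk of 30%, so 35 × 0.30 = 10.5 events occur in each arm.

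| Assumed attribution probability, arm A / arm B | Recorded events, A / B | Recorded risk ratio | Share of all events with no record |
|---|---|---|---|
| 0.5 / 0.5 | 5.25 / 5.25 | 1.0 | 50% |
| 0.6 / 0.4 | 6.3 / 4.2 | 1.5 | 50% |
| 0.8 / 0.4 | 8.4 / 4.2 | 2.0 | 40% |
| 0.4 / 0.8 | 4.2 / 8.4 | 0.5 | 40% |

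At a true risk of 20%, the 0.8 / 0.4 case gives 5.6 and 2.8 recorded events out of 7 in each arm. At 40% it gives 11.2 and 5.6 out of 14. The ratio stays at 2.0.

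If every event is recorded and relatedness is a separate field, attribution no longer affects the count of all events, and the expected ratio in each row is 1.0.

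**The case against.** The strongest reply is that this is a condensed article. Forms, elicitation questions and relatedness fields usually sit in the full protocol, and the SPIRIT items are said to be in a supplement that is not shown. The text does not say that other events are discarded, and the qualifier could grammatically apply to health issues alone. Pain, the most likely complaint, is scored at every session without anyone judging its cause.

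Part of this stands. The exclusive reading is natural but inferred, and the pain scores do cover a good share of pain worsening. What does not stand is that a fuller document would simply fill a gap. The sentence states a rule, and a full protocol that recorded all events would have to depart from it.

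A reader might also infer four stronger points that the documents do not support:

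- *That the unblinded delivery team decides attribution.* The recorder is a researcher who audits the assessment team. Who judges cause is not stated, and neither is that person's blinding. The Section 5.2 statements concern outcome assessment.
- *That IG2 events are over-recorded by 1.5 or 2.67 times.* That would require attribution to rise in proportion to contact, which nothing in the article shows. Of IG2's 32 hours, 20 are mindfulness sessions. Extra events truly caused by extra sessions would be a real effect of the arm. Missed home-practice events would act in the opposite direction.
- *That events in detraining are certain to be lost.* The pain scales and the clinical survey at t2 may catch some of them.
- *That a planned harms comparison is invalid.* Section 4 plans no formal between-arm test of harms.

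**Conclusion.** The concern holds in a limited form. As written, Section 2.4 makes a judgement of cause the condition for entering the adverse-event record, in a trial without blinded assessment and with no blinding stated for the recorder. Any safety statement or descriptive comparison by arm could therefore be biased. Events left out at entry cannot be recovered from the adverse-event record, and the other sources would recover only some of them.

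The documents fix neither the direction nor the size of the bias. The recorded risk ratios of 0.5 to 2.0 in the illustration rest entirely on assumed attribution probabilities. The conclusion itself rests on the natural reading of one sentence and on no other provision in the article calling for all events to be collected. The change should be made, but it does not touch the primary or secondary efficacy analyses.

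**What to change.** Reword the sentence in Section 2.4 so that:

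1. all adverse events are recorded in every arm regardless of presumed cause, including those during home practice and the detraining period;
2. they are elicited with the same standard question at the exercise or usual-care sessions common to all three arms, and at t1 and t2, so that the extra mindfulness sessions do not create extra opportunities to report;
3. relatedness is judged afterwards and kept as a separate field beside severity and resolution, if possible by someone unaware of the arm;
4. all events and related events are both reported by arm.

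The cost is one reworded sentence, one added question on the session log and at the two later assessments, and slightly longer logs. Sample size and efficacy analyses do not change.
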